### Treatment intensity

Treatment intensity is a critical factor for optimizing speech motor learning [18]. There are a number of ways in which intensity can be operationalized [19] including the number of practice trials or teaching episodes per session (i.e., 'dose'; [10, 11]), number of total practice trials/teaching episodes over a period of time (i.e., ‘cumulative intervention intensity’; [20]), and frequency of treatment sessions (i.e., ‘dose frequency’; [21–23]). Investigations of treatment intensity in children with CAS reveal improved treatment outcomes when participants produce a higher number of trials per session [10] and when a greater number of practice trials are produced for a smaller stimulus set [11]. For instance, in a production frequency study of two children with CAS receiving integral stimulation treatment, Edeal and Gildersleeve-Neumann [10] reported better treatment outcomes for targets that were practiced 100 + times during each session compared to those practiced 30–40 times.

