During DTTC treatment sessions, a small set of treatment targets are practiced using a modified block schedule. A total of five words or phrases (i.e., treatment targets) will be practiced within any given treatment session with one treatment target produced individually at a time in either a small block (i.e., 15–24 words per block) or a large block (i.e., 25–40 words per block). The objective of each session is to achieve 2–3 blocks for each treatment target. There is a minimum of 50 productions per session required for each participant although we anticipate that there will be between 100–200 productions per session for each participant. In each session the clinicians will practice 5 treatment targets with 2–3 blocks per targeted word/phrase (total of 10–15 blocks across the session) with small blocks containing 15–25 productions and large blocks containing 25–40 productions. Clinicians will record each time a target was practiced and whether it was practiced in a small or large block.

At the beginning of each block, the clinician elicits a target in direct imitation and then uses clinical decision-making to determine the appropriate level of the temporal hierarchy depending on the degree of support needed for the targeted word/phrase (most support = *Simultaneous;* least support = *Spontaneous*). Practice may advance from *Simultaneous Production* to *Direct Imitation* once the child has accurately produced a treatment target 5–15 times at a regular rate of speech and the clinician has introduced varied prosody. After achieving 5–15 accurate productions at *Direct Imitation* with varied prosody, a target will be practiced at the level of *Delayed Imitation*. Practice will advance from *Delayed Imitation* to *Spontaneous Production* once a child has accurately produced a target 10–15 times with varied prosody. Once a word/phrase has been accurately produced at the level of *Spontaneous Production* 10/10 times across three consecutive sessions, that treatment target will be graduated out of active practice. The clinician will then refer to the Treatment Target bank to determine the next word or phrase item to include in treatment.

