Growth curve modeling considers change over time as an underlying latent process. In analyzing this process, a trajectory of change over time is established for each individual in a sample, and therefore, characteristics of the trajectory (e.g., slope) may vary across individuals and are treated as latent variables. These latent variables describe parameters of change and may be treated as independent, dependent, control, or mediating variables and be compared across groups. Specifically, the growth curve model will allow us to (a) compare the treatment effect between Low Dose Frequency treatment and High Dose Frequency treatment groups during the treatment stage; (b) compare groups on maintenance effects during the post-treatment stage; (c) explain variations in change by incorporating various predictors. The growth curve model will also allow us to model flexible patterns of change in time such as quadratic and piecewise forms. Analyses will be conducted using Mplus software 5.0 [33].

Throughout our modeling process, we will carefully consider potential confounders that should be added to the model as covariates, such as severity of impairment, number of blocks practiced per session, age, and sex of the children. In the presence of attrition, an intention to treat analysis will be performed and compared with the analysis done on the “per protocol” population whenever possible. Baseline characteristics of the completed and withdrawn participants will be compared to prevent selection bias in the conclusions. In addition, internal validity (i.e., how well the randomization worked to create similar study groups) will be checked by comparing the groups on relevant measures using analyses of variance.

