### Data cleaning and preparation

Data will be securely stored and transferred in SharePoint folders. Trained research assistants will enter data into spreadsheets using participant identifiers. All data will be reviewed for valid values/data entry errors, outliers, and the extent and patterns of missing data. Consistency and logic checks that constitute standard review/cleaning procedures will be applied. The distributions of these measures across sessions will be summarized. Descriptive statistics will be used to describe measures at different periods in the study. Growth curve models allow us to quantify change from pre- to post-treatment and post-treatment to maintenance by interacting the treatment effect with time. Effect sizes for treatment will be compared between Low Dose Frequency treatment and High Dose Frequency treatment. The growth curve of each individual participant will be fit through random effect components, which control intra-participant correlation introduced by repeated measures. Covariates will also be included to control for any covariate imbalance between different treatment groups.

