### Potential limitations

As noted above, assessments and treatment in the proposed study will be conducted by community speech-language pathologists. Although engaging community clinicians in this study will help to increase the application, external validity, and translation of this research, it may result in potential limitations as well. To start, DTTC is considered a dynamic and individualized treatment that relies on the clinician’s ability to monitor and cue the child to promote speech accuracy. The clinical experience of our community clinicians will vary which could introduce clinician effects. However, the randomization of participants to groups should help to minimize any effects of the clinician or clinical environment. In addition, to help address the varied expertise of the clinician partners working in this study, all clinicians will be required to undergo 20 h of training focused on assessment and treatment protocols and study procedures. Fidelity measures will also ensure that all clinicians, regardless of their prior experience, will adhere to the study protocols. Additional training and guidance will be given if needed. Clinicians will also meet in a group with the research team twice per month for ongoing training and problem-solving as needed. There is also the possibility that children may be challenged with the intensive treatment schedule and 60-min sessions where they are engaged in structured practice. As DTTC is focused on conscious practice of speech production, children may become frustrated and fatigued during sessions. As part of the clinical training and group meetings, strategies have been presented to support clinicians in their ability to maintain engagement, build trust and rapport, and practice at optimal challenge levels for each individual child. Group meetings will also offer clinicians the opportunity to review clinical cases and approaches for supporting children across the treatment phase.

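### Blocks practised per session is listed as a confounder but arises after randomisation; adjusting the arm comparison for it can bias the dose-frequency effect if the schedule changes blocks

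*Protocol article*

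**What the plan says.** In the protocol article, the statistical analysis plan section describes a growth-curve model that compares the two arms during treatment and again during maintenance. It then names candidates for adjustment: "potential confounders that should be added to the model as covariates, such as severity of impairment, number of blocks practiced per session, age, and sex". The data cleaning and preparation section adds a rule: "Covariates will also be included to control for any covariate imbalance between different treatment groups". That rule is not restricted to variables measured before allocation.

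The DTTC protocol section shows when blocks come into being: "Clinicians will record each time a target was practiced and whether it was practiced in a small or large block". The number is a goal, not a fixed quantity: "The objective of each session is to achieve 2–3 blocks for each treatment target". The amount of practice may vary widely: "There is a minimum of 50 productions per session required for each participant although we anticipate that there will be between 100–200 productions per session".

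**The concern.** A confounder of a treatment comparison must influence which treatment is received. Under randomisation, nothing that happens after allocation can do that. Blocks per session is produced in the treatment sessions, so it belongs with the consequences of allocation, or at least with the events that follow it.

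Two things can go wrong if it enters the arm comparison:

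- **Part of the effect is removed or added.** If one schedule leads to more or fewer blocks and blocks drive learning, holding blocks fixed takes that route out of the estimate.
- **A non-causal path is opened.** The background section names attention, severity and resilience as possible drivers of response. Such child factors could also determine how many blocks a child completes. Conditioning on blocks then links the arm to these factors, and randomisation no longer protects the comparison.

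The imbalance rule aggravates this. A difference in blocks between arms is what an effect of the schedule would look like, yet under the rule it becomes a reason to adjust. The stakes are practical: the discussion section says that, if treatment effects are shown but no group difference is detected, schedule can follow resources and preference. A distorted coefficient could hide a real difference or create a false one.

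**Working it through.** **Inputs from the documents**

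- Blocks are observed after randomisation (DTTC protocol section, quoted above).
- Schedule to blocks is a possible route: "children may be challenged with the intensive treatment schedule and 60-min sessions where they are engaged in structured practice" (potential limitations section). No size is given.
- Practice to outcome: the treatment intensity section reports "improved treatment outcomes when participants produce a higher number of trials per session". That evidence concerns trials rather than blocks, and no size usable here is given.
- Effect size 0.35 and 30 children per arm (targeted enrollment section). The 0.35 is used only to set the scale. The 80% power stated with it plays no part in this point, and it cannot be reproduced because the simulation variances are not given.

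The plan gives no figure for the effect of adjustment, so there is none to reproduce.

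**Assumed quantities (not in the documents), in within-arm SD units**

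- *a*: effect of high versus low frequency on blocks per session
- *b*: effect of blocks on gain
- *c*, *d*: effects of an unmeasured child factor on blocks and on gain
- *T*: total effect of assignment, set at 0.35

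**Formula.** With blocks scaled to unit variance within arm, the within-arm slope of gain on blocks is *b* + *cd*. The model without blocks estimates *T*. The model with blocks estimates

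adjusted effect = *T* − *a*(*b* + *cd*)

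**Results for *T* = 0.35**

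| *a* | *b* | *c* = *d* | Calculation | Adjusted effect |
|---|---|---|---|---|
| 0 | any | any | 0.35 − 0 | 0.35 |
| +0.3 | 0.3 | 0 | 0.35 − 0.3 × 0.30 | 0.26 |
| +0.3 | 0.5 | 0.4 | 0.35 − 0.3 × 0.66 | 0.15 |
| −0.3 | 0.3 | 0 | 0.35 + 0.3 × 0.30 | 0.44 |
| −0.5 | 0.5 | 0 | 0.35 + 0.5 × 0.50 | 0.60 |
| −0.5 | 0.5 | 0.4 | 0.35 + 0.5 × 0.66 | 0.68 |
| +0.3 | 0 | 0.5 | 0.35 − 0.3 × 0.25 | 0.28 |

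A simulation over *a* = −0.5, −0.3 and +0.3, *b* = 0.3 and 0.5, and a shared factor of 0 or 0.4 gave 0.15 to 0.67. The 0.68 in the table becomes 0.67 if blocks are not rescaled after the shared factor is added (0.35 + 0.5 × (0.5 + 0.16/1.16) = 0.67). The last row shows that bias can arise even when blocks have no effect of their own, through the shared child factor alone.

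**Check at the trial's size.** In 4,000 simulated trials of 30 per arm, with *b* = 0.3:

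| *a* | Adjusted, no shared factor | Adjusted, *c* = *d* = 0.5 |
|---|---|---|
| 0 | 0.35 | 0.35 |
| +0.3 | 0.26 | 0.18 |
| +0.5 | 0.20 | 0.07 |
| −0.3 | 0.44 | 0.51 |

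With a true effect of zero and the shared factor present, the adjusted estimate was −0.17 (*a* = 0.3) and −0.27 (*a* = 0.5). Leaving blocks out returned 0.34 to 0.35 in every scenario with a true 0.35, and 0.00 under the null.

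**Could the trial's own data settle whether *a* is zero?** Not closely. The standard error of the difference in mean blocks is √(1/30 + 1/30) = 0.26 SD, so a 95% interval reaches about ±0.51 SD. Shifts of 0.3 SD, and even 0.5 SD, could lie inside it.

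**The case against.** Several counter-arguments have force.

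- **Adjustment is not fixed.** The text promises only to consider these covariates. A reader might infer that the plan commits to adjusting for blocks; it does not. Still, it labels blocks a confounder and nowhere confines it to a secondary analysis.
- **The schedule may not change blocks.** Both arms have one-hour sessions, five targets, the same goal of 10 to 15 blocks and the same 90% fidelity standard. A reader might infer from "children may become frustrated and fatigued during sessions" that high frequency will lower blocks. The documents do not support that: the sentence ties fatigue to conscious practice, which is common to both arms. Only the sentence before it mentions the intensive schedule, and it does not mention blocks. So the accurate claim is that adjustment can bias, not that it does.
- **Reach.** The covariate list follows the growth-curve text. The quasi-Poisson effect size for the primary outcome names no covariates, so the point should not be extended to every model.
- **A legitimate use exists.** The plan also wants the growth model to explain variation in change through predictors. Blocks can serve there, as exploration.
- **Holding practice constant could be the aim.** The current study section defines constant cumulative dosage as 24 completed sessions, not equal blocks. Nor would equal blocks mean equal practice, since a block may hold from 15 to 40 productions.
- **Detail may sit in an unseen analysis plan.** That excuses an incomplete covariate list. It does not excuse naming a post-randomisation variable as a confounder.

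**Conclusion.** The point holds in a limited form. Blocks per session is misclassified: it is a possible mediator and cannot confound the randomised comparison. If it enters the growth-curve comparison of the arms, the estimate can move either way when the schedule changes blocks: from 0.35 to about 0.15 to 0.67 in the main illustration, and as low as 0.07 under the stronger assumptions of the second. When the schedule has no effect on blocks, the estimate stays at 0.35.

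Every path strength is assumed, so these figures show direction and possible size, not an expected bias. A reader might infer that bias is certain; the documents do not show that the schedule alters blocks. Even in the no-effect case, however, blocks would not be a confounder, so control of bias never justifies including it.

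**What to change.** 1. In the statistical analysis plan section, remove blocks per session from the covariates of the between-arm comparison.
2. Limit adjustment to prespecified baseline variables: severity, age and sex. Add baseline accuracy only in models that do not already include the baseline probes as outcomes; in a growth curve that models those probes it would duplicate them.
3. In the data cleaning and preparation section, restrict the imbalance rule to baseline variables.
4. Report blocks and productions per session by arm as delivered dose. Use them otherwise only in a labelled exploratory mediation or predictor analysis.

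The cost is a few sentences of text. No new data are needed: clinicians already record the blocks, and the baseline variables are already collected.

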### Data cleaning and preparation

Data will be securely stored and transferred in SharePoint folders. Trained research assistants will enter data into spreadsheets using participant identifiers. All data will be reviewed for valid values/data entry errors, outliers, and the extent and patterns of missing data. Consistency and logic checks that constitute standard review/cleaning procedures will be applied. The distributions of these measures across sessions will be summarized. Descriptive statistics will be used to describe measures at different periods in the study. Growth curve models allow us to quantify change from pre- to post-treatment and post-treatment to maintenance by interacting the treatment effect with time. Effect sizes for treatment will be compared between Low Dose Frequency treatment and High Dose Frequency treatment. The growth curve of each individual participant will be fit through random effect components, which control intra-participant correlation introduced by repeated measures. Covariates will also be included to control for any covariate imbalance between different treatment groups.

#### Missing values

Missing data will be documented, as well as reasons as to why the data is missing (e.g., experimenter error, missed session, poor audio quality) where available. Upon completion of data collection, we will evaluate whether missing data is a random occurrence or due to a specific reason. If a recurring reason for missing data is determined, this variable will be coded and included within statistical modeling as a co-variate.

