## Methods and design

The proposed work is a multisite Phase III parallel-group RCT that aims to investigate the outcomes of DTTC in children with CAS (ages 2;6 to 7;11) and determine whether dose frequency impacts response to treatment. Participants will be randomly assigned to receive DTTC treatment at a low dose frequency (2x/week over 12 weeks) or high dose frequency (4x/week over 6 weeks). Group assignment will be performed using concealed randomization. All assessments and treatment will be provided by community SLPs throughout North America. All of the clinicians working on this study will undergo a rigorous application process, as well as extensive training including numerous applied activities. They will receive ongoing feedback from the investigators, who are SLPs with expertise in CAS, throughout the study to ensure high adherence to experimental protocols and fidelity to the operationalized assessment and treatment approaches.

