Clinical research conducted in a lab often has the benefit of employing research assistants to help manage audio-visual recording for probes and treatment sessions, which helps to ensure high-quality recordings and to minimize data loss. By contrast, the community clinicians employed in this study will have to manage clinical care along with recordings and other logistics, which may result in occasional data loss if a video recording is not started appropriately or if there is a technical difficulty. To prevent missing data, all probes will also be audio recorded with a separate device as backup in case the video recording fails. Other safeguards will also be in place to ensure that clinicians provide assessments and treatment in a standardized way while also managing the many other requirements of research data collection. Examples of these safeguards include emails or text messages sent to clinicians prior to probe sessions as a reminder of tasks that need to be completed, daily session checklists indicating all activities to be completed during each session, and a study manual that provides detailed, operationalized protocols and procedures.

Difficulty with recruitment is also a potential challenge. While CAS is a relatively rare disorder occurring in only 1/1000 children [3], by including over 20 community clinicians across North America, we should be able to recruit the 60 participants required for the proposed study. We anticipate that some families may prefer to come 4 times per week while others may view that as too much of a burden and would prefer to come only twice a week. Given that this is an RCT, family preference will not be a factor in group assignment. To help support families who may be concerned about transportation and/or childcare of their other children while they are bringing a participant to treatment, a stipend of $40 will be provided for each session the child attends.

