This study will compare two different treatment schedules and, consequently, it is imperative that children attend according to the prescribed schedule. While missing sessions due to illness such as COVID-19 cannot be avoided, it is possible to schedule study participation around other commitments such as vacations and holidays. To avoid preventable absences from treatment and follow-up sessions and ensure adherence to the study protocol, each clinician will work through the entirety of the study schedule with families prior to conducting baseline testing. Families will sign off in agreement to all dates from baseline through the 12-week follow-up before these activities begin.

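### Entering a recurring reason for missing data as a model covariate recovers no missing outcome and can bias the arm comparison when the reason arises after randomisation

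*Protocol article*

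**What the plan says.** The Missing values section of the protocol article first commits to documenting missing data and "reasons as to why the data is missing (e.g., experimenter error, missed session, poor audio quality) where available". It then fixes the timing of the assessment: "Upon completion of data collection, we will evaluate whether missing data is a random occurrence or due to a specific reason". The consequence follows directly: "If a recurring reason for missing data is determined, this variable will be coded and included within statistical modeling as a co-variate".

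The Statistical analysis plan section names a growth curve model with random intercept and slope. If there is attrition, it plans an intention-to-treat analysis set beside a per-protocol one. It also says: "Baseline characteristics of the completed and withdrawn participants will be compared to prevent selection bias in the conclusions".

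The randomised factor is the visit schedule: two sessions a week for 12 weeks, or four a week for 6 weeks (Methods and design). Under Potential limitations the authors expect that "some families may prefer to come 4 times per week while others may view that as too much of a burden", accept some absence ("While missing sessions due to illness such as COVID-19 cannot be avoided"), and foresee recording problems, "which may result in occasional data loss if a video recording is not started appropriately or if there is a technical difficulty".

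**The concern.** Two separate problems arise from the rule as stated.

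First, a term for the reason does not supply the unobserved scores. It shifts the fitted mean, or slope, of children who carry the flag. It carries no information about what their missing probes would have shown.

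Second, the listed reasons are events at visits, not baseline traits. Apart from any tied only to baseline probes taken before allocation, they occur after randomisation. The trial randomises how often families attend, so missed sessions could plausibly differ between arms. They could also go with slow progress, fatigue or frustration. Holding such a variable fixed compares children who are no longer alike by randomisation, and the resulting contrast is not the intention-to-treat effect. Because what counts as recurring is decided once the data are in, the choice of covariate is also data-dependent.

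At stake is the comparison of the two schedules, which is the purpose of the trial.

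**Working it through.** The plan attaches no figure to this rule, so there is none to reproduce. The check has two parts.

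**1. What the covariate can do at each level of coding.**
- *Whole probe occasion lost.* The reason exists only where the score is absent. Among observed rows the flag is constant, so a design with intercept, arm and flag has rank 2 of 3 and the flag coefficient cannot be estimated.
- *Part of an occasion lost.* P2 and P7 to P10 comprise two or three probe sets, and each set has 50 items (Probe data and its subsections). If one set or some items fail, a session-level flag can vary among observed rows. It can then be estimated, but it still does not fill in the lost scores.
- *Child level* (for example, had missed sessions). The flag can be estimated. The arm contrast then becomes conditional on a post-randomisation event.

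**2. What a child-level flag does to the arm contrast.** This was examined by simulation. Taken from the protocol are 30 children per arm and, as one of the two direct effects tried, the figure 0.35. Everything else is assumed: 7 probes on a time scale from 0 to 1; SDs of 0.8 (intercept), 0.6 (slope) and 0.5 (residual); the last 3 probes missing if flagged; 4,000 runs per scenario. Each child's slope was estimated and the slopes compared by weighted regression, as a simple stand-in for the growth model. Where the flag depends on arm, its log-odds are −1.8 in one arm and −0.6 in the other for a child of average slope:
- 1/(1 + e^1.8) = 0.142
- 1/(1 + e^0.6) = 0.354

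Mean estimated arm difference in slope:

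| Flag depends on | Direct arm effect | Complete data | Available probes, no flag term | Available probes plus flag term |
|---|---|---|---|---|
| neither arm nor outcome | 0.35 | 0.350 | 0.348 | 0.348 |
| arm only | 0.35 | 0.352 | 0.353 | 0.352 |
| child's slope only | 0.35 | 0.351 | 0.353 | 0.352 |
| arm and child's slope | 0 | −0.001 | 0.050 | 0.110 |
| arm and child's slope | 0.35 | 0.350 | 0.399 | 0.461 |
| arm, and missed sessions lower the slope by 0.4 | 0.35 | 0.265 | 0.309 | 0.349 |

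The Monte Carlo error of an entry is about 0.229/√4000 = 0.004, so the differences in the lower three rows are not noise.

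- *Rows 1 to 3.* When the flag is tied to only one of arm and outcome, or to neither, the term changes nothing.
- *Rows 4 and 5.* When the flag is tied to both, the term adds 0.110 − 0.050 = 0.060 and 0.461 − 0.399 = 0.062 to a bias already present. In the arm with more flags, flagged children are less strongly selected for slow progress and unflagged children more strongly selected for good progress. Both strata therefore favour that arm.
- *Row 6.* The total effect is 0.35 − 0.4 × (0.354 − 0.142) = 0.265. Adjusting returns 0.349, close to the direct effect, because the part that runs through missed sessions has been removed. This row needs missed treatment sessions, not merely missing probes. The two can coincide, since P4 to P6 are taken at the start of treatment sessions 7, 13 and 19 (Treatment phase).

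In no simulated scenario did the flag term reduce bias by more than simulation error.

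**The case against.** The case on the other side has real force on several points.

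- Two of the three listed reasons, experimenter error and poor audio quality, are technical. A failed recording does not alter a child's gain, and if it is unrelated to arm the covariate does no harm. This stands, and it confines the bias essentially to reasons of the missed-session kind.
- A reader might infer that the rule displaces likelihood-based handling. It does not: it adds a term to a growth model that stays in place, and the abbreviation list includes maximum likelihood.
- A reader might infer that the rule operates precisely when missingness differs between arms. The trigger is any recurring reason; arm is not mentioned.
- A reader might turn the 10% attrition allowance into 6 of 60 children without late probes. Targeted enrollment describes those 6 as possible additional recruits, and Group allocation provides for substitution of withdrawals, so the text does not support that count.
- It is tempting to multiply assumed path strengths and quote the product as a share of the planned 0.35. No such strengths appear in the document, and 0.35 is scaled by the square root of the model variance, which is not shown to be the SD of gain.
- The protocol mitigates absence: families agree all dates beforehand, a stipend of $40 is paid per session, and probes have backup audio. The illness absences it mentions need not depend on arm. This lowers the likely amount of missing data but does not make the rule sound.
- A stated missing-at-random assumption, auxiliary variables and a sensitivity analysis commonly belong in an analysis plan that is not shown here. Their absence is not the point. The covariate rule is something the protocol does state.
- Leaving the covariate out is not bias-free either: row 4 shows 0.050 without it.

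**Conclusion.** The point holds in conditional form. The protocol fixes an adjustment that recovers no missing outcome. For a reason that depends on both the assigned schedule and the child's progress, the adjustment can bias the arm comparison and departs from the planned intention-to-treat analysis. For technical loss unrelated to arm and outcome it is harmless and useless.

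The size for this trial cannot be derived from the document, because the associations of reason with arm and with outcome are unknown. The simulated shift of about 0.06 is an illustration under assumed parameters. Its flag rates of 14% and 35% are well above the protocol's 10% attrition allowance, which is itself a different quantity. The direction is also open: if the other schedule produced more missed sessions, the shift would reverse.

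A baseline predictor of missingness used as a covariate, or a pattern-mixture model averaged over patterns, would be legitimate, but the Missing values section describes neither.

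**What to change.** Replace the covariate sentence in the Missing values section with a statement to this effect:

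- The growth curve model is fitted by maximum likelihood to all available probes of all randomised children.
- Covariates added on account of missingness are restricted to baseline predictors. Severity, age, attention and resilience are already collected at the eligibility assessment.
- The arm effect is not adjusted for reasons for missingness that arise after randomisation. These reasons are tabulated by arm.

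A simple sensitivity analysis for data missing not at random, such as a delta shift applied to probes missing after withdrawal, may be added. It would address the bias that remains when missingness depends on unobserved progress.

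The cost is a change of wording, plus one further model run if the sensitivity analysis is included. No additional data are needed.
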